3.13 Continuation of chemoprophylaxis in the health centre

Study subjects will receive their monthly chemoprevention at their local health centre under direct supervision by staff of the health centre who will be identified by the health centre and trained to take this important role in the study. At this first OPD attendance, mothers/guardians will receive clear oral instructions as to where to go for the prophylaxis. In addition, written instructions in English and the mother/guardian’s preferred local language will be provided to them. Health centre staff will be provided with a list containing the study number, photographs and randomisation group of each study subject. Study subjects will be observed for 30 minutes after dosing and if vomiting occurs within 30 minutes, the dose will be repeated. For infants and young children, the tablets will be crushed and mixed with water. S/P (tablets containing 500 mg sulfadoxine/ 25 mg pyrimethamine) will be given at an approximate dose of 1.25 mg pyrimethamine/25 mg sulphadoxine per kg. Enrolment of patients will start in July and surveillance will continue until end of malaria transmission season.

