**3.4 Enrolment of children**

Children will be enrolled from the paediatric unit of the Royal Victoria Teaching Hospital, Banjul, the MRC Hospital, Fajara, Brikama Health Centre or Essau Health Centre during the first year of the study. The study will be extended to WEC clinic in Sibanor during the second year . Study subjects will be enrolled by non-coercive methods if they met the inclusion criteria and had none of the exclusion criteria.

Inclusion criteria:

1. Age: 3 months to 9 years.
2. Haemoglobin less than 7 g/dL
3. Residence within 30 km of the study centre and availability for the duration of the study period.
4. Informed consent to participate in the study given by the parent or guardian.

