3.9 Discharge from hospital

Study subjects will be individually randomised into either the S/P or the placebo group in a 1:1 fashion at the time of discharge from hospital, although chemoprophylaxis will not be started for another week as the children are likely to have received antimalarials whilst in hospital. Randomisation will be in blocks. Block size will be selected to enhance blinding and maintain balance in the treatment allocation ratio as recruitment progresses

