3.12 Randomisation

Children will be individually randomized into either the SP or the placebo group in a 1:1 ratio, using permuted blocks of 12 generated by computer using the STATA program. Blocks will not split across centres. Tablets (enough for 6 doses) will be packed into envelopes bearing the randomization number. The next envelope in sequence will be assigned to the child at the time of their admission to hospital. The randomisation code will be kept in sealed opaque envelopes by the local safety monitor and the MRC Laboratories accountant who alone will know the code, which associates each treatment group with either S/P or placebo.

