# 3.14 Morbidity surveillance during the rainy season

Study subjects will be followed throughout the rainy season. Mothers/guardians will be encouraged to take their child to the RVH OPD clinic or the health centre identified as being closest to their home at any time after discharge if the child becomes unwell. Project staff will be based at each of these health centres, initially to identify children in the trial and to ensure that they are seen, properly investigated and treated promptly by health centre staff. At each visit axillary temperature will be recorded using a digital thermometer. A dipstick for diagnosis of malaria will be used to guide treatment if fever (axillary temperature of  37.5°C) or history of fever within the previous 48 hours is present. In addition, a thick blood smear for malaria parasites will be collected for subsequent confirmation of the diagnosis. Filter paper sample to test for S/P resistance will be collected from all malaria cases detected during morbidity surveillance. Study subjects with documented fever (axillary temperature of  37.5°C) or history of recent fever and malaria parasitaemia will be treated with S/P and chloroquine. The treatment of study subjects seen at the health centres will be the carried out by health centre staff in accordance with national guidelines. Study patients needing admission will be referred to RVH paediatric unit or the MRC ward. The Health centre ambulance will be used to transfer study patients referred for admission but if this is not available, the field worker will arrange for the use of MRC transport as soon as possible. Study children admitted to the RVH or MRC hospital will be fully documented.

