## **4.2 Local Safety Monitor**

A local safety monitor will be appointed. His role will be to support the clinical investigators and to act as a link between the investigators and the DSMB. All serious adverse events suspected to be related to trial medication will be reported to him in his capacity as a liaison to the DSMB.

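### Section 3.13 lists each child's randomisation group for health-centre staff, which either contradicts or weakens the masking set up in section 3.12

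*Protocol*

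**What the plan says.** Section 3.13 has the monthly doses taken at the child's local health centre, "under direct supervision by staff of the health centre". It then states: "Health centre staff will be provided with a list containing the study number, photographs and randomisation group of each study subject". It does not say whether the group is shown as a code or as the drug.

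Section 3.12 places the randomisation code with the local safety monitor and the MRC accountant, "who alone will know the code, which associates each treatment group with either S/P or placebo". It also says that each child's tablets, enough for six doses, are packed in advance in an envelope marked with the randomisation number. Allocation is 1:1, "using permuted blocks of 12 generated by computer using the STATA program", with each block kept within one centre and envelopes used in sequence.

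On illness during the season, section 3.14 says: "The treatment of study subjects seen at the health centres will be the carried out by health centre staff". A dipstick guides treatment, and a smear is kept for later confirmation.

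Section 3.4 names health centres among the first-year recruiting sites: "Brikama Health Centre or Essau Health Centre during the first year of the study".

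**The concern.** Staff who dose and manage trial children should not hold group membership unless they need it. Nothing in the protocol shows that they need it here, because the drug is already packed by child.

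Section 3.18 counts outpatient attendances with malaria and hospital admissions with malaria as secondary endpoints, and the Summary calls the former an important one. Both depend partly on judgement at the health centre: whether a history of fever is elicited, whether a child is tested and treated, and whether the child is referred. Section 3.22 gives a power statement for a 32% reduction in clinical malaria from 131 expected control episodes. That is a difference of about 42 episodes (131 × 0.32 = 41.9), so differential ascertainment or management by group would matter. Once the lists are distributed the disclosure cannot be undone, and no later analysis can reliably correct for it.

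**Working it through.** **Step 1: the two readings of the list.** The protocol states no figure for this point, so the check starts by setting sections side by side.

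- *Group means the drug.* Sections 3.9 and 3.12 both name the groups as S/P and placebo, and section 3.13 does not mention a code. On this reading health-centre staff hold the allocation, and section 3.12 cannot be right that only two people know it.
- *Group means a code.* Section 3.12 speaks of a code that links each treatment group to a drug, which fits a list showing labels only. Masking then lasts until one child's drug is learned or inferred. From that moment every listed child with the same label is unmasked. An identifier unique to each child would confine the event to that child.

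**Step 2: could a drug be inferred?** Under section 3.13 tablets are crushed in water for infants and young children. Under section 3.14 trial children with malaria receive open-label S/P with chloroquine, so known S/P is at hand for comparison. The protocol does not say that the placebo matches S/P in appearance or taste. This does not show that they differ, only that the text gives no assurance. A listed label also lets staff tally malaria attendances by group.

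**Step 3: is the label needed?** No stated task uses it. The photograph and study number identify the child, and the numbered envelope identifies the tablets.

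**Step 4: predictability of allocation.** Inputs from section 3.12: ratio 1:1, block size 12, so m = 6 per arm, with blocks kept within a centre and used in order. Assumption: the person guessing knows every earlier label in the current block, in order, and always guesses the label used less so far.

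- Expected correct guesses per block = m + 2^(2m−1)/C(2m, m) − 1/2 = 6 + 2048/924 − 0.5 = 7.72. As a share, 7.72/12 = 64.3%, against 50% with no knowledge.
- Expected allocations known with certainty at the end of a block = 2m/(m+1) = 12/7 = 1.71. As a share, 1.71/12 = 14.3%.

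Exact enumeration gives the same values. The same enumeration for other block sizes:

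| Block size | Correct guesses | Certain |
|---|---|---|
| 4 | 70.8% | 33.3% |
| 6 | 68.3% | 25.0% |
| 8 | 66.6% | 20.0% |
| 12 | 64.3% | 14.3% |

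Without the labels the guess rate returns to 50% and no allocation is known in advance.

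**The case against.** The strongest reply is that sections 3.12 and 3.13, read together, most naturally describe a coded label. A reader might infer that masking is broken outright. That holds only if the list names the drug, which the protocol leaves open but does not state. This part of the reply stands.

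A reader might also infer that one unmasking event reveals every child in the trial. That needs exactly two labels. Section 3.12 does not say how many there are, and its wording would also fit several codes per arm.

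A third tempting inference is that recruiters can guess the next allocation. The 64% and 14% are ceilings. Lists go to the child's local health centre, whereas blocks run by enrolling centre, so a list need not reproduce a block. A project doctor assesses eligibility (section 3.5), and nothing says that list holders enrol children. Health-centre dosing follows a first dose given a week after discharge (section 3.11), so the newest allocations may not yet be listed. Under a code, only the label could be predicted, not the drug. Brikama and Essau both recruit and are health centres, so overlap there is plausible, but it is not stated.

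Nor do the documents support treating the block size as an error. Section 3.9 says: "Block size will be selected to enhance blinding and maintain balance in the treatment allocation ratio". Twelve is less predictable than the smaller sizes shown above. Varying the size would be a preference.

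The same applies to the code holder. Section 4.2 says of the local safety monitor: "His role will be to support the clinical investigators". The protocol gives this role no part in enrolment or outcome assessment, and the code is kept in sealed opaque envelopes. It also does not say that health-centre staff attribute adverse events, so no bias there can be claimed.

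Finally, the endpoints have objective anchors: measured temperature, dipstick, confirmatory smear, parasitological case definitions and WHO criteria for severe malaria. The primary endpoint is a haemoglobin measured at a survey where a study physician examines the child. These limit the harm but do not remove it, because fever history and referral remain partly subjective. None of these replies gives a reason for the label to be on the list.

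**Conclusion.** The point holds in a limited form. Section 3.13 discloses group membership to staff with no stated need for it. If the label is the drug, sections 3.12 and 3.13 contradict each other and these staff are unmasked. If it is a shared code, masking is weakened, because one disclosure spreads to all listed children with that label.

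The exposure lies mainly in the secondary endpoints of malaria outpatient attendances and admissions. The primary haemoglobin endpoint is less exposed, although unequal testing or treatment through the season could still affect it. The documents give no basis for putting a number on the bias.

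Prediction of allocations is a subsidiary risk, bounded at 64% correct and 14% certain under the full-knowledge assumption, and most plausible at the recruiting health centres. The conclusion does not depend on the block size or on who holds the code.

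**What to change.** In section 3.13, delete the randomisation group from the contents of the health-centre list. Identify each child by study number, photograph and numbered envelope only. If the study number differs from the randomisation number on the envelope, list the latter in place of the group so that staff can match child to tablets. If the label was meant to supply a repeat dose after vomiting, spares marked with the child's randomisation number would serve without revealing the group.

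This brings section 3.13 into line with section 3.12 and largely removes any risk of predicting allocations within blocks. The cost is a wording change and a reissued list. The envelopes already exist, and neither the randomisation scheme nor the sample size changes.

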### Chemoprophylaxis and intermittent preventive treatment

Antimalarial chemoprophylaxis in endemic countries has been shown to reduce malarial morbidity, school absenteeism, and all cause mortality but it is no longer advocated because of concerns over its possible effect on the development of resistance, logistics constrains and its potential effect on the development of natural immunity. Chemoprophylaxis can lead to loss of acquired immunity or delay its development and this can potentially cause an increase in episodes of clinical malaria when the intervention is withdrawn. To take advantage of the protective effects of chemoprophylaxis whilst reducing its possible adverse effect on the development of natural immunity to malaria, intermittent preventive treatment (IPT) with an effective an antimalarial has been advocated. IPT involves giving a full treatment dose of an antimalarial drug at specific times, regardless of the presence or absence of malaria parasites. Since treatment is only given on an intermittent basis, this intervention is less likely to interfere with the development of immune responses than sustained chemoprophylaxis. The results of trials conducted using IPT have so far been encouraging.

To determine whether children who had experienced an attack of severe malarial anaemia might benefit from a limited period of chemoprophylaxis, we undertook a pilot trial in 1994 in which MaloprimR (pryrimethamine/dapsone) chemoprophylaxis was given after children had been discharged from hospital. Children who received chemoprophylaxis had fewer episodes of malaria. However, there was no significant difference in the mean haematocrit between those who received chemoprophylaxis and the control group at the end of the follow-up. This was most likely due to the fact that chemoprophylaxis was only started after the end of main malaria transmission season when there was hardly any transmission of malaria taking place26

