### **3.2 Malaria in The Gambia**

Transmission of malaria in The Gambia is seasonal. The climate is typical of sub-Sahelian Africa, with a long dry season which lasts from November-June, followed by a relatively short rainy season from July-October. Rainfall averages about 600 mm per year. Morbidity and mortality from malaria follow this pattern, both occurring more frequently during the rainy season, with a peak in the month of October. *P. falciparum* is the dominant species, being responsible for all severe diseases and for over 95% of clinical attacks. A few cases of clinical malaria are caused by *P. malariae;* *P. ovale* is seen rarely. In rural areas, children experience 0.5-1.0 clinical attacks of malaria a year. Over 90% of clinical attacks occur during the rainy season. Parasite and spleen rates in children aged 1-4 years range from 25% -50%. Acute respiratory infection and malaria are the most common causes of death in children who survive the first month of life. Malaria causes about 4% of deaths in infants and 25% of deaths in children 1- 4 years of age.

Chloroquine is still the officially recommended first line treatment for uncomplicated malaria, but sulphadoxine/pyrimethamine is used widely and quinine is used for the treatment of severe malaria. Anti-malarials can be purchased in several pharmacies in Greater Banjul. Bed nets are used widely in rural areas and The Gambia Government makes permethrin available at a modest cost at the beginning of the malaria transmission season.

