3.11 First OPD visit after discharge from hospital

One week after discharge, study subjects enrolled in the study will be asked to return to the OPD clinic for routine assessment. At this visit a fingerpick blood samples will be collected for haemoglobin measurement and thick blood film examination for malaria parasite. The first dose of trial medication will be given during this visit. Any medical condition detected during the visit will be treated.

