**(d) Time-table**

Timetable

|  | 2003 | | | | | | | | | | | | 2004 | | | | | | | | | | | |
| --- | --- | --- | --- | --- | --- | --- | --- | --- | --- | --- | --- | --- | --- | --- | --- | --- | --- | --- | --- | --- | --- | --- | --- | --- |
|  | 1 | 2 | 3 | 4 | 5 | 6 | 7 | 8 | 9 | 10 | 11 | 12 | 1 | 2 | 3 | 4 | 5 | 6 | 7 | 8 | 9 | 10 | 11 | 12 |
| SCC & ERC submission |  | x | x |  |  |  |  |  |  |  |  |  |  |  |  |  |  |  |  |  |  |  |  |  |
| Enrolment |  |  |  |  |  |  | x | x | x | x | x | x |  |  |  |  |  |  | x | x | x | x | x | x |
| Morbidity surveillance |  |  |  |  |  |  | x | x | x | x | x | x |  |  |  |  |  |  | x | x | x | x | x | x |
| Mortality surveillance |  |  |  |  |  |  | x | x | x | x | x | x |  |  |  |  |  |  | x | x | x | x | x | x |
| Monthly SP treatment |  |  |  |  |  |  | x | x | x | x | x | x |  |  |  |  |  |  | x | x | x | x | x | x |
| End of season survey |  |  |  |  |  |  |  |  |  |  |  | x |  |  |  |  |  |  |  |  |  |  |  | x |
| Dry season visit |  |  |  |  |  |  |  |  |  |  |  |  |  |  |  |  | x |  |  |  |  |  |  |  |

Dose 1 of SP/ placebo

Hb &BF

Monthly SP/placebo at hospital/HC

Passive surveillance, Hb & BF

Clinical assessment

BF & Hb

Clinical assessment, treatment,

± transfusion, Hb & BF

Enrolment, admission

Discharge from Hospital/ HC

Monthly hospital/HC visit

Hospital/HC visit if unwell

Day 7 OPD

visit

End of malaria season

survey

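### Enrolment stays open through December, the month of the primary-endpoint survey, with no last-entry date, so late entrants dilute the treatment effect by an unquantified amount

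*Protocol*

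**What the plan says.** - **Enrolment window.** Section 3.13: "Enrolment of patients will start in July and surveillance will continue until end of malaria transmission season". This fixes the start of enrolment and the length of surveillance, but not the end of enrolment. The timetable fills that gap: enrolment is marked in months 7 to 12 of 2003 and again of 2004.
- **Survey.** The timetable row "End of season survey" is marked in month 12 of each year. Sections 3.15 and 3.18 make the haemoglobin taken then the primary endpoint (proportion below 7 g/dL). Section 3.20 analyses it by intention to treat.
- **Start of trial drug.** Section 3.11, describing the outpatient visit one week after discharge: "The first dose of trial medication will be given during this visit". Doses are then monthly. Section 3.6 also has children receive a standard SP dose on leaving hospital, without distinction by arm.
- **Season.** Section 3.2 describes a climate "with a long dry season which lasts from November-June, followed by a relatively short rainy season from July-October", puts the peak of malaria in October, and adds: "Over 90% of clinical attacks occur during the rainy season".
- **Pilot.** The background explains the earlier trial's lack of a haematocrit difference by the fact that "chemoprophylaxis was only started after the end of main malaria transmission season when there was hardly any transmission of malaria" was taking place.
- **Entry threshold.** Section 3.4 requires haemoglobin below 7 g/dL, the same cut-off as the endpoint.

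**The concern.** The endpoint is read at one calendar point for everybody, while entry is staggered over six months that include the month of the reading. Time on trial drug therefore runs from about five months or more for a July entrant to days, or nothing, for a late-December one.

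Three features of the protocol shrink the contrast between arms for the latest entrants:

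1. They can have one trial dose at most.
2. The SP given at discharge covers the placebo arm too. If one dose protects for about the monthly interval on which the regimen is built, that cover spans the whole period to the survey.
3. Transmission is mostly over by then, on the protocol's own description.

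In addition, entry and endpoint share a threshold. With only weeks between the two measurements, a value still below 7 g/dL partly reflects slow recovery from the admission episode, which allocation can hardly change. Such children bring events unrelated to treatment into both arms, and the sample size makes no visible allowance for them.

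**Working it through.** **Step 1. Doses possible before the survey.** The first trial dose falls at admission + hospital stay + 7 days, and the second a month later.

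- Admission on 1 December: first dose after 8 December, second in January. At most one dose before a December survey, and none if admission is late in the month.
- Admission in early November: first dose around mid-November, second around mid-December. One or two doses, depending on the survey date.

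**Step 2. Reproduce the plan's figure.** Section 3.22 gives 1200 children, 15% dropout, control prevalence 20%, a 34% reduction and 80% power. The 5% level is stated there for the malaria endpoint; I assume it is two-sided and applies here too.

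- Analysed per arm: 600 × 0.85 = 510.
- p1 = 0.20; p2 = 0.20 × 0.66 = 0.132; difference d = 0.068; mean proportion p̄ = 0.166.
- se0 = √[2 p̄(1 − p̄)/n] = √(0.27689/510) = 0.02330.
- se1 = √{[p1(1 − p1) + p2(1 − p2)]/n} = √(0.27458/510) = 0.02320.
- Power = Φ[(d − 1.96 se0)/se1] = Φ(0.96) = 83%.

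With continuity correction the power is 81% and the required enrolment is 1172. The stated 1200 therefore reproduces, with little margin above 80%.

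**Step 3. Dilution.** Let a share f of analysed children be late entrants with no treatment effect and the same 20% prevalence, and let the 34% hold in the rest. The average reduction is then 34% × (1 − f). The fourth column instead leaves late entrants out without replacing them: 510 × (1 − f) per arm, with the full 34%. All powers are without continuity correction.

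| Late share f | Average reduction | Power, all included (510 per arm) | Power, late entrants left out | Enrolment for 80% power, all included |
|---|---|---|---|---|
| 0 | 34.0% | 83% | 83% | 1104 |
| 5% | 32.3% | 79% | 81% | 1233 |
| 10% | 30.6% | 74% | 79% | 1386 |
| 1/6 | 28.3% | 67% | 76% | 1633 |
| 1/3 | 22.7% | 47% | 66% | 2622 |

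The shares are assumptions. One sixth (200 of 1200) is December alone and one third (400 of 1200) is November plus December, both under even accrual over six months.

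**Step 4. When does leaving them out help?** Let late entrants have a reduction r instead of zero. The average reduction is 34% × (1 − f) + r × f. Setting the power of the two options equal and solving for r gives break-even values of 18.1%, 17.8%, 17.5% and 16.5% at f = 5%, 10%, 1/6 and 1/3. Leaving late entrants out gains power only if their own effect is below about half of the assumed 34%.

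**The case against.** **Accrual should fall after October.** Section 3.1 names malaria as the main cause of anaemia in these children, and section 3.2 puts its peak in October. A reader might infer from the calendar that a third of the children enter late and that power is 47%. The documents do not support that: they give no monthly accrual, and even accrual sits badly with an October peak. The 5% and 10% rows may be nearer the truth. This stands.

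**Short follow-up may already be planned for.** In section 3.22, 131 control episodes at 0.1 per month imply 131/0.1 = 1310 child-months, which is 2.2 months per child on 600 or 2.6 on 510. That fits staggered entry. The 34% might likewise be meant as an average over all entrants. This is possible, but the protocol does not say so, and the anaemia calculation contains no term for follow-up time.

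**Zero effect in late entrants is the extreme case.** A reader might infer that nothing is transmitted in November and December. Section 3.2 leaves up to a tenth of attacks outside the rains, and the timetable continues dosing and surveillance through December. 'Little' transmission is the supportable word.

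**The pilot is not being repeated.** There, prophylaxis began only after the main season; here dosing starts in July. Only the late subset resembles the pilot.

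**No bias arises.** Late entry affects both randomised arms alike, and the Summary's stated question is treatment for the remainder of the season. This stands: the cost is power and a smaller average effect, not validity.

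**Conclusion.** The overlap between enrolment and the endpoint survey is in the timetable, and nothing elsewhere in the protocol limits it. December entrants can contribute almost no information on the treatment effect, and an analysis plan cannot give them exposure time. The consequence is dilution of unknown size. If late entrants show no effect and the 34% applies to the others, power is below 80% already at a 5% late share (79%), and is 74% at 10%. The figures of 67% and 47% need even accrual and are probably too pessimistic. With continuity correction the corresponding powers are 76%, 71%, 64% and 44%, from a starting value of 81%.

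The case is firm for December entrants and weaker for early-November entrants, who may have two doses. It should be fixed because the remedy is cheap, but it does not put the trial's validity in question.

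**What to change.** State in section 3.13 and the timetable a last-entry date for each year, set at a fixed interval before the survey long enough for a treatment contrast to build up; at the least, no child should enter in the survey month. Alternatively, keep enrolment open but define the primary analysis set by admission date, which treatment cannot influence, and report later entrants separately. In either case, restate in section 3.22 the expected number of children and the detectable reduction for that set, and say whether the 34% is meant as an average over all entry dates. Hospital admissions by month from earlier years, if available, would show how large the late share is likely to be.

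The cost is protocol wording and somewhat fewer children in the primary analysis. Power rises on balance only if the effect in the excluded children would be below about 17%. That is plausible for December and less certain for early November, which argues for a modest cut-off.
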